### 27.1 Radiotherapy Data and principal component analysis

The dose values for the lungs, heart, and substructures will be based on cumulative DVH values. Each DVH will be sampled from zero to 70 Gy in 2 Gy increments, resulting in 35 numbers representing each cumulative DVH. For each patient, there will be DVHs available for ten structures, resulting in 10 DVHs available for each patient, consisting of 350 numbers. The included structures are the lungs (combined left and right), whole heart, left and right atrium, left and right ventricle, and the four coronary arteries: right coronary artery (RCA), circumflex artery (CX), left anterior descending (LAD) and left main coronary artery (LMCA).

Two different models will be utilized. The primary model will consider DVH volumes for the lungs, whole heart, and heart chambers, while the second model will incorporate DVHs for the lungs, whole heart, and coronary arteries. Each model will thus be based on six DVHs. It is important to note that the values within a DVH are highly correlated with each other, as DVH curves are non-increasing functions. Therefore, a PCA analysis (decomposition) will be performed on the DVH values for the entire patient cohort to address the significant correlations and reduce the number of degrees of freedom.

A PCA analysis is a non-supervised learning method that can be applied to the data without the risk of leaking information into the predictive model. Before conducting the PCA analysis, the mean value for each DVH value across the patient cohort is calculated. This mean value is then subtracted from the original values to obtain patient-specific values representing the deviation from the cohort values. Finally, these modified values are used to establish the primary components within the data (PCA). Each principal component is a linear combination of the original DVH values and is ordered in decreasing order based on the variance of the original data that it describes.

For the current trial, the principal components selected will account for at least 95% of the variance in the original data. However, a maximum of eight principal components will be included in the model selection process to ensure efficient parameter selection based on the best-subset method (as described in section 27, Analysis Methods). Consequently, the PCA method reduces the initial 350 correlated numbers per patient to a maximum of 8 uncorrelated values. Once the principal components are determined, the corresponding values for each component per patient are calculated. These values then become part of the model selection process alongside other clinical parameters.

If the computer time at “Forskermaskinen” shows to take above one day, we might be forced to reduce to a maximum of six components.

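### The single PCA over lung and cardiac DVHs yields no heart-dose HR with lung dose held fixed, although the primary hypothesis is read from such an HR

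*SAP*

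**What the plan says.** Section 27.1 defines ten structures with 35 DVH values each, and two models. For the first, "The primary model will consider DVH volumes for the lungs, whole heart, and heart chambers"; the second takes lungs, whole heart and the four coronary arteries. "Each model will thus be based on six DVHs".

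The reduction is described once: "a PCA analysis (decomposition) will be performed on the DVH values for the entire patient cohort". The only preprocessing given is centring: "This mean value is then subtracted from the original values". Neither scaling nor the volume unit (percent or cm³) is stated. The retention rule is that "the principal components selected will account for at least 95% of the variance in the original data", with at most eight components, or six if computing time is too long. The section concludes that "the PCA method reduces the initial 350 correlated numbers per patient to a maximum of 8 uncorrelated values".

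Three other places bear on this:

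- Section 8 asks about lung, heart and substructure dose, and forces no variable into the selected model.
- Section 12 states the primary hypothesis for dose to the heart and its substructures, and reads it from an HR that differs from one.
- Section 27 promises figures explaining the chosen components. It gives no rule for assigning a component to an organ and no heart contrast adjusted for lung dose.

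**The concern.** Lung dose is the obvious rival explanation for an association between heart dose and survival, because both come from the same beams. To answer Section 12, the analysis needs a heart term with lung dose held fixed. The plan does not provide one. Each component combines all six DVHs, and no lung term is guaranteed in the model. That component scores are uncorrelated with one another does not make a heart-heavy score uncorrelated with lung dose.

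At stake is whether a lung-dose effect could be reported as a heart-dose effect, or the reverse. A second question is whether the retention rule keeps enough lung dose to tell the two apart.

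**Working it through.** **Dimension count.** Ten structures × 35 values = 350, which reproduces the SAP's figure for all available numbers. (A 0–70 Gy grid in 2 Gy steps gives 36 points, or 35 with one end dropped.) Each model uses six structures: 6 × 35 = 210. So 350 is not the input to either model's PCA.

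**Why uncorrelated scores do not adjust for lung dose.** Suppose the log hazard depends only on lung dose L. In the linear approximation, the coefficient of the first component is cov(L, PC1)/var(PC1). Because the components are mutually uncorrelated, adding the others leaves this unchanged. It is non-zero whenever L is correlated with PC1, and it does not vanish because PC1 loads mainly on the heart.

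**Illustrative simulation of that mechanism.** From the SAP: 644 patients (patient characteristics table), six DVHs × 35 points, centring only, the 95% rule, and a cap of 8 or 6. Assumed: DVH shapes and organ spreads, lung–heart dose correlation of 0, 0.3 or 0.6, a true lung effect of HR 1.35 per SD with no heart effect, and 80% deaths. There were 40 runs per setting, so the Monte Carlo standard error is at most √(0.25/40) = 0.08. The largest squared lung loading of PC1 was 0.034, so PC1 was at least 96% cardiac throughout. How often the leading cardiac component had p<0.05:

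| Assumed lung–heart correlation | Component alone | All retained components in the model |
|---|---|---|
| 0 | 0–10% | 0–15% |
| 0.3 | 25–57% | 25–62% |
| 0.6 | 80–97% | 88–97% |

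**How much lung dose is kept.** The lung share of pooled variance is SD²(lung) divided by the sum of SD² over the six structures. The SAP gives no SDs. Assume, in percentage points of relative volume, lungs 5–9, whole heart 12–18, chambers 10–32 and coronary arteries 15–42.

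- Primary model, extremes: 25/(25 + 324 + 4 × 1024) = 0.6% and 81/(81 + 144 + 4 × 100) = 13%.
- Second model, extremes: 25/(25 + 324 + 4 × 1764) = 0.3% and 81/(81 + 144 + 4 × 225) = 7.2%.
- Independent uniform draws over these ranges: medians of about 2.3% and 1.3%, with the share below 5% in about 98% and nearly 100% of draws. If the four chambers share one SD, the primary-model figure falls to 85%.

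A share below 5% means the 95% rule would permit losing all lung variance. It does not mean the rule does so. Retention in the simulation:

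| Model | Lung variance kept, cap 8 | Lung variance kept, cap 6 |
|---|---|---|
| Primary (chambers) | 86–91% | 59–91% |
| Second (coronary arteries) | 24–91% | 2–80% |

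A second illustrative simulation gave lower figures: about 65–86% in the primary model with eight components, and 3–65% across both models with six. In the first simulation the coronary model needed about 10–11 components to reach 95%, so the 95% rule and the cap conflicted there.

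**Volume unit.** With DVHs in cm³ and assumed organ volumes, the imbalance reverses: lungs carried 84–94% of pooled variance, and only 38–51% of chamber variance was kept.

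**The case against.** The strongest defence is that Section 8 asks about lung, heart and substructure dose together and selects models by cross-validated performance. For prediction, a joint centred PCA is legitimate, and leaving every variable unforced is a deliberate choice. This stands, and it is why the fix should not force lung terms into the selection. It does not cover Section 12, which states a heart-dose hypothesis and reads it from an HR. The planned figures show loadings; they do not adjust.

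Three stronger readings are tempting, and the documents support none of them:

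- *No component HR can be attributed to the heart.* A leading component can be almost purely cardiac by loading. If lung and heart dose were uncorrelated, its HR would be readable as a heart effect; the simulated rates at correlation 0 are about what chance gives. The SAP neither shows nor assumes such a correlation structure.
- *The 95% rule will discard lung dose.* PCA drops low-variance directions, not organs. In the primary model with eight components, most lung variance survived in both simulations.
- *Because the PCA reduces 350 numbers, both models share the same components.* Section 27.1 plainly describes two models of six DVHs each. The 350 is best read as the count of all available values carried forward, which is a wording slip.

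The cm³ case is also only a possibility. The unit for the PCA is unstated, but the patient characteristics table reports lung and heart volumes at dose in percent.

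**Conclusion.** The point holds in limited form. As described, a component HR does not estimate the effect of heart dose at fixed lung dose, yet Section 12 rests the primary hypothesis on it. This follows from the stated method whenever lung and heart dose are correlated. That the PCA is joint and unscaled is inferred from the only procedure Section 27.1 describes; requiring mutually uncorrelated scores fits that reading.

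The size is not known for this cohort. Under the assumptions above, misattribution runs from about chance level at correlation 0 to 80–97% at 0.6. Partial loss of lung dose is possible, not certain. It is of concern mainly in the coronary model or under the six-component fallback, and depends on dose spreads the SAP does not give. The 350 against 210 discrepancy needs no assumption and is editorial.

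**What to change.** In Section 27.1:

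1. State that DVHs are in relative volume (%).
2. Run one PCA on the lung DVH (35 values) and a separate one on whole heart plus chambers (primary) or whole heart plus coronary arteries (second), 5 × 35 = 175 values.
3. Keep the total number of components over both blocks within the existing cap of eight (or six), state how it is divided between the blocks, and state that the cap takes precedence over the 95% rule.
4. Replace 350 with the number each model uses, 35 + 175 = 210.

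In Section 27, keep best-subset selection as planned with nothing forced. In addition, report the HRs of the selected cardiac components from a Cox model that includes the lung components. Base any statement about heart dose under Section 12 on that lung-adjusted estimate.

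The cost is a few sentences of SAP text, a small change to the PCA code and one extra Cox model per dose model. Keeping the joint cap means the best-subset search is no larger than planned. The downside is that lung and cardiac scores are no longer mutually uncorrelated, so the adjusted intervals may be wider. Section 2 states that no heart-dose analysis had been done when the SAP was completed; a revision made while that is still true remains prespecified.

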## 28. Missing data

Missing data will be reported in Table 1 (Patient Characteristics). Multiple imputations will be performed before each Bootstrap for the best subset analysis. The imputation method is based on Multivariate Imputation by Chained Equations (The MICE package in the R statistical software).

## 29. Additional analyses

No further analyses are planned for this cohort.

## 30. Harms

Not relevant

## 31. Statistical software

Statistical analyses will be performed in STATA/BE 17.0 and R- statistical software version 4.2.

Radiotherapy data analysis and principal component analysis are performed on MATLAB- Mathworks version 2023a.

| 5                                                                 | 90 (14%)    |
| 6                                                                 | 57 (9%)     |
| RT technique                                               |             |
| 3D-CRT                                                            | 57 (9%)     |
| IMRT                                                              | 264 (41%)   |
| VMAT                                                              | 323 (50%)   |
| Heart dose                                                 |             |
| Mean Heart Dose, Gy (IQR)                                         |             |
| Heart V5Gy, %                                                     |             |
| Heart V30Gy, %                                                    |             |
| Lung Dose (IQR)                                            |             |
| Lung V5Gy, %                                                      |             |
| Lung V20Gy, %                                                     |             |
| Lung Mean Dose                                                    |             |
| Cardiac disease before RT                                  |             |
| Hypertension                                                      |             |
| Diabetes                                                          |             |
| Myocardial infarction                                             |             |
| Valvular disease                                                  |             |
| Pulmonary Embolism                                                |             |
| Pulmonary Heart Disease                                           |             |
| Cerebral Infarction                                               |             |
| Heart failure                                                     |             |
| Arrhythmia, including
conduction disorders, AFLI,
and AFLA. |             |
| Pericardial disease                                               |             |
